### Randomization

After the baseline interview, participants are assigned to either treatment or control groups using a restricted randomization scheme. This scheme achieves balance between the two groups at all points during the study period. Prior to the beginning of the study, a permuted block randomization schedule for 420 subjects was created using the RANTBL and RANUNI functions in SAS to generate blocks with varying sizes of 8, 10, or 12 and random numbers for group assignment. After every block, there will be an equal number of intervention and control participants. This process ensures that over the course of the study, 210 women will be assigned to each of the two study conditions. It also reduces potential confounding effects (e.g., seasonal variation) which might occur due to the rolling recruitment process.

### Theory and content of intervention

*WCAC *is based on the Center for Managing Chronic Disease model of self-regulation for disease management, a framework that has been informed by social cognitive theory [18]. Participants are introduced to a self-regulatory problem-solving process, which is designed to help them engage more effectively in their asthma management. This process, which reflects the key components of the self-regulation model, include the following steps: 1) **Identifying a problem **in asthma management (participants are offered a list of potential asthma-management problems, including those associated with their sex, gender roles, culture and other relevant challenges; recommendations from the participant's physician are also reviewed at this stage); 2) **Observing **oneself, one's environment, and one's pattern of symptoms so as to understand both the influences on the problem and the way those influences might be ameliorated; 3) **Setting an asthma-management goal**; 4) **Developing a plan or strategy **to achieve the goal; and 5) **Tracking progress, reacting appropriately, and establishing suitable rewards **for success. Participants are guided by the counselor through a period of self-observation using a peak-flow meter and symptom diary, along with a checklist of physical activity, environmental factors, and other potential precipitants to asthma exacerbations. This observation period enables them to see the barriers and facilitators to achieving desired management practices and outcomes. Telephone sessions last 45 minutes to 1 hour and take place approximately every two weeks. Table 2 provides an overview of the content of each session. Importantly, the content of the intervention also reinforces the priority messages put forth by the National Asthma Education and Prevention Program's Guidelines Implementation Panel [19]: appropriate use of inhaled corticosteroids, reviewing asthma control, having an asthma action plan, periodic follow-up visits with clinician as appropriate, and allergen and irritant exposure control.

**Table 2 T2:** *Women of Color and Asthma Control *intervention: Overview of program session content

Session	Examples of topics, and self-regulation phases addressed:	Goals for participant	Other content
1	Use of peak flow meter (PFM); tracking symptoms, medications and triggers; allergies.	Self-observe using asthma diary (mail copy of diary data back to health educator).	
	
2	Review PFM and symptom diary.	Use review to identify symptom patterns and triggers. Continue self-observation.	
	
3	Review PFM and symptom diary; review therapeutic plan provided by physician. Identify a management goal and develop plan to achieve goal.	Develop a plan for addressing the problem area and reaching goal. Carry out steps of the management plan.	Discussions of sex-, gender- and culture-related influences on asthma and asthma management are integrated into each session.
	
4	Review progress toward goal and adjust plan as needed.	Assess progress, fine-tune plan, and continue toward problem resolution.	
	
5	Review progress toward goal and consider next steps (e.g., refine plan, choose new problem, etc.). Discuss reward and benchmarks of progress.	Achieve goal as appropriate, apply problem solving process to new/different management problems.	

### Control condition

The control condition will consist of usual care from the UMHS or a BCBSM provider. At the UMHS, this care consists of evidence-based clinical practice and adherence to National Asthma Education and Prevention Program (NAEPP) guidelines for asthma diagnosis and treatment, and development of asthma action plans. Emphasis is also placed on patient education about disease processes, importance of trigger avoidance, and the development of a partnership for asthma care. Standardized asthma education kits are available in all UMHS clinic sites, and clinic personnel have been trained in their use by a certified asthma educator. Of note, sex-specific, gender-role, or culturally-related issues are not systematically or routinely addressed during the clinical encounter or in educational materials. All *WCAC *participants are sent basic asthma education materials ("Controlling Your Asthma" booklet from the American College of Chest Physicians) upon completion of the baseline interview.

### Outcomes and measures

Data is collected from participants via telephone interviews with trained research assistants. Data is collected on paper and then entered twice into Qualtrics, a secure online survey program, to ensure accuracy. With the participants' permission, an audio recording of the interview is also made to verify data accuracy and completion. Data collection takes place at three time points: baseline (before randomization), 12 months, and 24 months.

The primary study outcomes are the *number of asthma-related Emergency Department (ED) visits *and the *number of overnight hospitalizations *in the last 12 months. These will be collected via self-report on telephone interviews, as well as from medical and billing records.

Other outcomes of interest include the following:

#### Frequency of daytime and nighttime asthma symptoms

(coughing, wheezing, shortness of breath, and chest tightness), over the past month, seasonally, and in the last 12 months.

#### Asthma Control Test [20]

This validated, five-item questionnaire assesses the effect of asthma on daily functioning, shortness of breath, nighttime asthma symptoms, rescue medication use, and overall self-rated asthma control over the last 4 weeks.

#### Mini Asthma Quality of Life Questionnaire [21]

This validated 15-item scale addresses the following four domains specific to adult asthma patients: 1) activity limitations; 2) symptoms; 3) emotional function; and 4) environmental stimuli.

#### Absenteeism activity days

In the previous 12 months, 1) total days when physical activity was limited because of asthma; 2) total days of missed work or school because of asthma.

#### Other health care utilization

In the previous 12 months, unscheduled clinic visits for urgent asthma treatment and scheduled clinic visits for asthma care.

#### Asthma self-regulation skills and self-efficacy

A scale was developed by the authors that measures the frequency with which participants engage in the self-regulatory behaviors of observations, judgments, and reactions as applied to asthma management; and also measures self-efficacy for each of these behaviors.

#### Sex/gender-specific management problems

This scale, used in previous work by the authors [15], measures the frequency of problems of asthma management related to hormonal cycles, sexual activity, urinary incontinence, and triggers associated with gender roles.

#### African-American-specific management problems

This scale, developed by the authors, measures the frequency with which participants experience asthma-management challenges that may be common among African American women (e.g., having numerous family responsibilities, physician communication, money concerns or worries).

Data is also collected on a wide array of demographic, health and psychosocial characteristics at all three time points.

### Analysis

Statistical testing will evaluate changes in the primary and secondary outcomes, and other outcomes of interest, over the course of the study, and assess differences in these changes as a function of participation in the intervention. Descriptive statistics will be computed for all outcomes, as well as sociodemographic and health characteristics, overall and for each study group (treatment and control). This will help determine whether the treatment and usual-care groups are equivalent prior to intervention, and how these groups differ at specific follow-up points (12 and 24 months after baseline). We will use mixed-effects models for the analysis of continuous outcome variables and generalized estimating equations (GEEs) for analyzing discrete outcomes. Pre-planned contrasts will examine the nature of change over time, including the timing and longevity of intervention effects. SAS Version 9.2 and IVEware (to multiply impute missing data) will be used for analysis [22,23].

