**Methods/Design:**

A randomized controlled trial will be used to compare a five-session asthma-management intervention with usual care. This intervention is delivered over the telephone by a trained health educator. Intervention content is informed by the principles of self-regulation for disease management, and all program activities and materials are designed to be responsive to the specific needs of African American women. We will recruit 420 female participants who self-identify as African American, and who have seen a clinician for persistent asthma in the last year. Half of these will receive the intervention. The primary outcomes, upon which the target sample size is based, are number of asthma-related emergency department visits and overnight hospitalizations in the last 12 months. We will also assess the effect of the intervention on asthma symptoms and asthma-related quality of life. Data will be collected via telephone survey and medical record review at baseline, and 12 and 24 months from baseline.

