### Sample size determination

The sample size of 420 at baseline (210 women in each treatment condition) was determined by power calculations using the primary study outcomes of ED visits and hospitalizations in the last 12 months, taking into account 30% attrition rate over 24 months and a loss of 5 women per group due to pregnancy. In previous work we observed that for ED visits and hospitalizations the treatment takes at least 12 months to reach full effect; thus, the sample size calculations for these outcomes were performed at 24 months. However, for the other outcomes, e.g. asthma symptoms and QOL, the intervention effect occurred during the first 12 months and the power calculations for these were performed at 12 months, which is the same or more conservative than 24 months.

The relatively rare occurrence of ED vists and hospitalizations for asthma requires a large sample size to detect clinical improvement over time. In previous work by the authors based on 364 participants with asthma, belonging to the intervention group was associated with a 75% reduction for hospitalization and 53% for ED visits with at least 80% power (alpha = 5%) at 24-month follow-up. We conservatively estimate a smaller reduction for the same two outcomes with a similar sample size and the same statistical power. An initial total sample of 420 and a final available sample of 286 will have sufficient power to detect a 32% improvement in the proportion of participants having at least 1 ED visit (42% in mean ED visits) and a 41% improvement in the proportion having at least one hospitalization (46% in mean hospitalizations). Note that these power calculations also ensure our ability to assess other important outcomes such as asthma symptoms and asthma quality of life.

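### The group test is framed as a difference in change with no baseline adjustment; fitted without a constraint at baseline, it gives up precision that the pre-randomization counts could supply

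*Protocol article*

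**What the plan says.** The abstract of the protocol article defines the endpoints: "The primary outcomes, upon which the target sample size is based, are number of asthma-related emergency department visits and overnight hospitalizations in the last 12" (the count thus covers the year before each interview). Outcomes and measures sets the schedule: "Data collection takes place at three time points: baseline (before randomization), 12 months, and 24 months". A pre-randomization value of each primary outcome is therefore available.

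The Analysis section states that testing will look at changes in the outcomes and "assess differences in these changes as a function of participation in the intervention". On models it says: "We will use mixed-effects models for the analysis of continuous outcome variables and generalized estimating equations (GEEs) for analyzing discrete outcomes". On contrasts: "Pre-planned contrasts will examine the nature of change over time, including the timing and longevity of intervention effects". A comparison at single visits appears only in the sentences on descriptive statistics, which are to show "how these groups differ at specific follow-up points (12 and 24 months after baseline"). Neither a baseline covariate nor a constraint on the baseline means is mentioned.

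Sample size determination gives detectable effects with 286 women at the end, for emergency department (ED) visits a "32% improvement in the proportion of participants having at least 1 ED visit (42% in mean ED visits"). It takes its power level from the authors' previous study, described as "with at least 80% power (alpha = 5%) at 24-month follow-up", and says that the same power applies here. It states no control rate, standard deviation, correlation, sidedness or test.

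**The concern.** In a randomized trial the two arms have the same expected baseline, so any observed baseline difference is chance. A difference in change that lets each arm have its own baseline mean subtracts that chance difference in full, and its sampling error enters the treatment contrast. Adjusting for baseline subtracts only the part that predicts the follow-up value.

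The primary events are described as fairly rare and the article allows for 30% attrition, so power is not plentiful. The baseline 12-month window and the window reported at 24 months are also a full year apart. That makes a low to moderate correlation plausible, though the article does not document one. At such correlations the loss is largest.

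**Working it through.** **Inputs from the article.** 210 women per arm; loss of 5 per arm for pregnancy; 30% attrition; 286 evaluable at 24 months; 80% power at alpha 5%.

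**Assumptions.** Two-sided alpha; equal variances at baseline and follow-up; rho over a range, since none is given.

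**1. The plan's own figure.** (210 − 5) × 0.70 = 143.5, rounded down to 143 per arm; 2 × 143 = 286. The evaluable number reproduces. The power does not, because no control rate is given. A simple two-sided comparison of two proportions with 143 per arm reaches 80% power for a 32% reduction only if the control proportion is about 51% (51% against 35%).

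**2. Variance of the treatment contrast, relative to a follow-up-only comparison.**
- Difference in change, baseline unconstrained: 2(1 − rho)
- Baseline-adjusted: 1 − rho²
- Ratio of the two: 2(1 − rho) / [(1 − rho)(1 + rho)] = 2/(1 + rho), which exceeds 1 for every rho below 1

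**3. Power, if a follow-up-only test has 80% with 286 women.** Power = Phi(2.802/√v − 1.960), where v is the relative variance from step 2 and 2.802 = 1.960 + 0.842. For example, at rho 0.3 the change contrast has v = 1.40, so 2.802/1.183 − 1.960 = 0.408 and power is 66%. Evaluable N for 80% power is 286 × v, rounded up.

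| rho | v, change | v, adjusted | ratio | power, change | power, adjusted | N for 80%, change | N for 80%, adjusted |
|---|---|---|---|---|---|---|---|
| 0.2 | 1.60 | 0.96 | 1.67 | 60% | 82% | 458 | 275 |
| 0.3 | 1.40 | 0.91 | 1.54 | 66% | 84% | 401 | 261 |
| 0.5 | 1.00 | 0.75 | 1.33 | 80% | 90% | 286 | 215 |
| 0.7 | 0.60 | 0.51 | 1.18 | 95% | 98% | 172 | 146 |

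**4. Check on a binary outcome.** The formulas in step 2 are for continuous data. A simulation of any ED visit against none (143 per arm, assumed control proportion 0.49, 32% reduction, 1,500 trials per setting) compared three analyses: the unconstrained change in log-odds with robust variance, logistic regression adjusted for baseline, and follow-up only.

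| correlation of the binary outcomes | change | adjusted | follow-up only |
|---|---|---|---|
| 0.33 | 66% | 82% | 78% |
| 0.49 | 77% | 88% | 79% |
| 0.65 | 89% | 94% | 77% |

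The pattern matches the formulas: adjustment has the highest power in each row, and its lead over change shrinks as the correlation rises.

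**The case against.** The strongest reply is that the article does not fix the model. A free group difference at baseline is inferred. The same sentence is compatible with efficient analyses. In a linear model with baseline as covariate, the group coefficient is identical whether the response is the change or the follow-up value. A longitudinal model with a common baseline mean also estimates a difference in change. Study hypotheses, moreover, expects the arms to differ at 12 and 24 months, so follow-up comparisons are contemplated, and the handling of baseline is often left to an analysis plan.

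Most of this stands, and it makes the point conditional on how the contrast is fitted. It does not remove the point. The article does state the target of testing, the natural reading is a difference in change, and the wording admits a wasteful model as readily as an efficient one.

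A reader might go further and infer that the planned test is weaker than the comparison behind the sample size. The article does not support that. Sample size determination names no test. That its calculation refers to 24 months fixes a time point, not a follow-up-only analysis, and it also speaks of improvement across time. Even if the calculation was follow-up-only, change is weaker only when rho is below 0.5. It is equal at 0.5 and stronger above (95% at rho 0.7 where follow-up-only has 80%).

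**Conclusion.** The point holds in conditional form. If the stated difference in change is fitted as an unconstrained group-by-time contrast, it is less precise than a baseline-adjusted contrast at every correlation below 1. Its variance is larger by about two thirds at rho 0.2, a third at 0.5 and 18% at 0.7. The size rests on the equal-variance approximation and on assumed correlations. The power figures rest further on a reference case of 80% for follow-up-only, which the article does not establish. A difference in change remains a valid estimate of the treatment effect in a randomized trial, so neither bias nor a false-positive problem is alleged. The change is worth making because it is a better use of data already being collected.

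**What to change.** State that the primary contrast is the 24-month comparison between groups, for ED visits and for hospitalizations, from the planned GEE with the baseline 12-month count as covariate. Alternatively, specify a model that includes baseline as a response with its mean constrained equal across arms. In a GEE that alternative needs a working correlation other than independence, or the baseline contributes nothing to the contrast. Take the same approach in the mixed models for symptom, control and quality-of-life scores. Keep within-arm change as description.

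It would also help to state the control rate, the test and any correlation behind the power figure, so that readers can see which comparison it refers to.

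The cost is wording only. The baseline values are already collected and can enter the planned multiple imputation; no visit, measurement or participant is added.

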### Process evaluation

Data will also be collected regarding key aspects of the intervention process. First, participants will be asked to complete a brief online or mail survey regarding their experience with the WCAC program (e.g., satisfaction with counselor, perceived improvement in asthma-management skills) when they have completed the series of telephone counseling sessions. This survey also includes items designed to assess participants' satisfaction with the culturally-relevant elements of the program (e.g., "If you were to participate in a program like this one again, how important would it be to you that your health educator be African American?"). Second, telephone counselors will keep logs of each phone session to track elements such as participants' goals and progress in the self-regulation process. Finally, all telephone counseling sessions are audio-recorded and a random subset are reviewed for their fidelity to the planned program content. This process data will be used to enhance understanding of program outcomes, and to inform modifications to future versions of the program.

## Discussion

While African American women with asthma are at higher risk than their Caucasian counterparts of poor asthma-related outcomes, no prior asthma-management intervention has been adapted to address their particular needs and cultural context. The current trial will answer the question: Does a program relevant to the gender and culture of the participants reduce the burden of asthma on a particularly vulnerable group? To do this, it will test the efficacy of the WCAC program in reducing asthma-related ED use, hospitalizations, and symptoms, as well as improving asthma-related quality of life. It will also provide important information about the receptiveness of participants to an intervention relevant in this manner. If shown to be efficacious, the WCAC program will represent one means of addressing persistent racial disparities in asthma outcomes.

## List of abbreviations used

ED: Emergency Department; WCAC: Women of Color and Asthma Control; PFM: peak flow meter; QOL: quality of life; SES: socioeconomic status; BMI: body mass index; UMHS: University of Michigan Health System; BCBSM: Blue Cross Blue Shield of Michigan.
